## Abstract

**Background:**

Angulated fractures of the distal forearm are very frequent lesions in childhood. Currently, there are no standard guidelines on whether these children should be treated conservatively with a cast; with reduction and a cast; or with reduction, pinning and a cast under anesthesia.

Minor prospective and retrospective studies have shown that the distal physis of the forearm possesses high remodeling capacity leading to reliable correction of malalignment.

The aim of this trial is to answer the question about whether operative and conservative treatment show equivocal results.

**Methods/Design:**

This is a prospective, multinational, multicenter, randomized, observer-blinded, actively controlled, parallel group trial, with 24 months of observation.

The primary objective of this trial is to assess whether or not the long-term functional outcome in remodeling patients is inferior to patients receiving closed reduction and K-wire pinning.

The trial should include 742 patients with acute fracture. The patients will be included in 30 medical centers in Germany, Switzerland and Austria.

All patients 5 to 11 years of age presenting at the emergency department with an angulated distal fracture of the forearm will be randomized online after informed consent.

The primary endpoint is the Cooney Score after 24 months. The secondary endpoint is the grade of radiological displacement at 12/24 months.

**Discussion:**

Therapy of angulated fractures is a matter of intensive debate. Primary manipulation and pinning under general anesthesia is recommended in order to avoid malalignment. No major study has proven the advantage of manipulation and pinning over immobilization alone. Should remodeling appear to be a safe alternative, manipulation under general anesthesia, K-wire pinning and removal of pins could be avoided, thus sparing significant costs.

**Trial registration:**

DRKS00004874, 30 October 2013.

## Background

Metaphyseal fractures of the distal forearm are the most frequent lesions in childhood and account for 20 to 25 % of all fractures [3, 6]. Half of these fractures are angulated, with the two bone segments remaining in contact.

Currently, there are no standard guidelines on how these patients should be treated. Treatment varies from simple immobilization to open reduction and plate osteosynthesis. Closed reduction of pediatric fractures commonly requires sedation and analgesia to achieve an anatomic reduction and to alleviate the child’s reaction to and recall of a painful and stressful situation. Inserted implants must be removed after bony healing and aneasthesia or sedation therefore is needed. Complications associated with procedural anesthesia include respiratory depression, hypoxia, hypotension, vomiting and aspiration [7, 16]. Therefore, some authors advocate nonmanipulative therapy for distal forearm fractures [8].

Primary closed reduction leads to secondary loss of reduction with the necessity of remanipulation under general anesthesia in >30 % of cases [15]. Although percutaneous K-wire pinning prevents redisplacement, effects on longer-term outcomes, including function have not been established [1, 13]. Inserted K-wired need to be removed.

Reliable remodeling of displaced radial fractures is often described, whereas the grade of possible remodeling differs in various publications [2, 10, 12, 14, 17]. In many uncontrolled or retrospective studies, although some children retained malalignment after an accident, after 2 years and until the age of 14, remodeling of the axis of up to 30° occurred due to growth.

Advantages of conservative therapy without manipulation are outpatient treatment, no need for anesthesia, cleaning of pins or wound control. Parents are often afraid of operations, and children, of manipulation while cleaning the pins. Disadvantages are the extended time of healing until remodeling is achieved and the visible angulation that can lead to questions and comments on incorrect treatment.

The advantage of the operation is the immediate transfer of the fracture into a stable anatomic position and less chance of secondary angulation. The disadvantage is the need of anesthesia for osteosynthesis, need for implant removal and inpatient treatment, as well as the cleaning of the pins or wound control to prevent infection.

### Primary objective

The primary objective of this trial is to compare whether patients from 5 to 11 years old with angulated fractures of the forearm present the same results in function and appearance after 2 years, no matter if they have been treated conservatively without reduction or operatively with reduction and K-wire osteosynthesis.

### Secondary objective

The secondary objectives of this trial are the assessment of safety and effectiveness and the satisfaction of patient and parents.

## Methods/Design

The protocol and all trial documents have been approved by the ethics committees responsible for the respective trial sites. The main vote was received from the ethical committee of the University Clinic Mannheim, faculty of the Ruperto Carola University of Heidelberg (code: 2013-544 N-MA). All ethical bodies that approved our trial are listed in Fig. 1.

**Fig. 1 Fig1:**
[figure not shown]
Ethical bodies

### Inclusion criteria

Patients meeting all of the following criteria will be considered for admission to the trial:Age 5 to 11 yearsDistal metaphyseal fracture of radius or complete distal metaphyseal forearm fracture23-M/2-3 or 23-E/1-2 (according to AO classification)Angulated radius or complete forearm fractures in the distal third of the boneAngulated physiolysis with or without wedge of the metaphysisAngulation up to 30°Age 5 to 7 years 15°-30°Age 8 to 11 years 10°-25°Informed consent of child and parents

### Exclusion criteria

Patients presenting with one of the following criteria will not be included in the trial:Torus fracturesComplete displaced fractures with shorteningOther osteosynthesis needed than K-wireNeurologic diseaseMetabolic bone diseaseNeurovascular injuriesMultiple trauma

### Discontinuation criteria

A patient will be discontinued from the trial for any of the following reasons:On request of the patient/parentsIf the physician comes to the conclusion that continuing the trial is harmful to the patient’s well-beingIf a treatment is needed that is not allowed in the protocolSerious adverse events that are related to the trialSafety reasons determined by the trial admission or the advisory board

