### Treatment

Group 1 (experimental/conservative): Plaster immobilization without any reduction for 4 weeks, the kind of plaster (Paris, cast, forearm, upper arm or sandwich) is to be determined by the treating clinic. As no reduction is performed, no anesthesia is needed. After the fracture is immobilized with the plaster, the patient will leave the emergency department.

Group 2 (control): Closed reduction under anesthesia, percutaneous K-wire osteosynthesis with one or two wires (through physis or Kapandji), plaster (Paris, cast, forearm, upper arm or sandwich) is to be determined by the treating clinic. No other form of osteosynthesis is allowed. After the operation, the patient is treated on the ward for 1 or 2 days.

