### Trial duration

The anticipated trial duration will be 60 months. Recruiting began in April 2014 and will be completed in March 2018. All patients will be monitored for 2 years.

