### Primary endpoint

The primary endpoint is the Cooney Score after 24 months. If there is a visible malalignment, an X-Ray will be performed to confirm the exact degree of malalignement.

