### Power calculation/analysis

All patients presenting a Cooney Score of at least 90 after 24 months and, if clinically obvious, a radiologic displacement not exceeding 5°, will be compared between treatment groups by calculating a one-sided 97.5 % confidence interval of the difference of rates according to Farrington and Manning [9]. If this interval is located completely above the noninferiority bound of -5 %, noninferiority of the experimental intervention will be claimed. The primary analysis population is the per-protocol population, comprising all randomized patients without major protocol violations and at least one Cooney score radiological displacement measurement after intervention.

The primary endpoint is the validated Cooney-Score. This score considers subjective (pain, strength, activity before and after trauma) as well as objective (range of motion) parameters and has been validated in several trials that also included children and adolescents. As it is assumed that differences between the treatment groups with respect to the Cooney Scores fully disappear at (and not clearly before) 2 years after surgery/immobilization, an earlier time was not chosen for primary analysis.

Cooney Scores will be calculated according to the standard approach of aggregating the single items.

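### The discontinuation rule takes children out of the trial for outcome-related reasons without separating end of treatment from end of follow-up, and it contradicts the promise of two years' monitoring for all.

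*Protocol article*

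**What the plan says.** - **Discontinuation criteria:** "A patient will be discontinued from the trial for any of the following reasons". The list covers a request by the family, a physician's judgement of harm, the need for a non-permitted treatment, a trial-related serious adverse event, and safety decisions. The wording is mandatory. There is no category for a child who leaves the allocated treatment but stays under observation.
- **Treatment:** the cast group has plaster for 4 weeks without reduction. The control group has closed reduction, K-wires and plaster. For the control group the section adds "No other form of osteosynthesis is allowed". Under Trial schedule, the pins come out at a visit 4 weeks later.
- **Trial duration:** "All patients will be monitored for 2 years".
- **Primary endpoint:** "The primary endpoint is the Cooney Score after 24 months".
- **Secondary endpoint:** second reduction, renewed K-wire fixation, growth disturbance and complications are outcomes to be recorded.
- **Power calculation/analysis:** "The primary analysis population is the per-protocol population, comprising all randomized patients without major protocol violations", who must also have at least one outcome measurement after the intervention. Success is a Cooney score of at least 90 at 24 months and, where malalignment is clinically obvious, displacement of no more than 5°. The arms are compared by a one-sided 97.5% "confidence interval of the difference of rates according to Farrington and Manning". Non-inferiority is claimed if the interval is "located completely above the noninferiority bound of -5" percentage points.

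**The concern.** Allocated treatment takes about 4 weeks of a 24-month observation period. For most of that period there is no trial treatment left to stop, so a site that reads the rule literally may well end the visits.

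Two of the triggers tend to mark a poor course. Whether the 24-month score is missing would then depend on how treatment went, and in a non-inferiority trial such losses can make the arms look more alike than they are. The section on trial duration says the opposite, so different sites could handle the same child differently.

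The article gives some reason to expect unequal removal. The Background says that pinning prevents redisplacement and that surgery leaves less chance of secondary angulation. The Trial schedule gives the cast arm an X-ray at 7 days to look for dislocation, while the control arm's next scheduled radiological check after surgery comes 4 weeks later. On the other side, the Background lists complications of anaesthesia, which could remove operated children. The net direction is not known.

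**Working it through.** **1. The texts side by side**

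| Question | Discontinuation criteria | Trial duration |
|---|---|---|
| Is a child followed after a non-permitted treatment or a related serious adverse event? | Leaves the trial | Observed for 2 years like every other child |

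Both statements cannot hold for the same child unless discontinuation means something narrower than its wording. The conflict with the Secondary endpoint section is only partial. A second reduction or renewed pinning can be recorded when it happens, and the article does not say that either is a non-permitted treatment. The only explicit prohibition is of other osteosynthesis, stated for the control group. What is not secured is the course after the event.

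**2. The plan's own figure**

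The article gives 742 children, 2 × 371. It states no success rates, power or dropout, so 742 cannot be strictly reproduced. With an assumed 95% success in both arms, 80% power and one-sided 0.025, the Farrington-Manning formula gives 334 per group, and 668 / 0.9 = 742.2 with an assumed 10% dropout (744 if each arm is rounded up). An assumed 96% success, 90% power and no dropout gives 746. So 95% is a reasonable illustrative rate, but it is an assumption. The point does not depend on it.

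**3. Size of the hidden difference**

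Assumptions: control success 0.95; 5% of the cast arm removed (0.05 × 371 = 18.55, about 19 children); the remaining cast children succeed at 0.95; no removal in the control arm. The observed difference is then 0. Let s be the success rate the removed children would have had:

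true difference = 0.95 × 0.95 + 0.05 × s − 0.95

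| s | Calculation | Hidden difference |
|---|---|---|
| 0.95 | 0.9025 + 0.0475 − 0.95 | 0 |
| 0.50 | 0.9025 + 0.0250 − 0.95 | −2.25 points |
| 0 | 0.9025 + 0 − 0.95 | −4.75 points |

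**4. Effect on the error rate, worst case**

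Assumptions: 371 per arm, true difference exactly at the −5-point margin, a share x of the cast arm removed, all of them failures, none removed from the control arm. With true cast rate p_E and control rate p_C, the observed cast rate is p_E / (1 − x) on 371(1 − x) children. By normal approximation:

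P(claim) = Φ[(p_E/(1 − x) − p_C + 0.05)/SE − 1.96]

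For p_C = 0.95, p_E = 0.90 and x = 0.02: observed cast rate 0.9184, observed difference −0.0316, SE = 0.0183, P = 0.17.

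| Removed from cast arm | About how many children | P(false claim), 95% v 90% | P(false claim), 90% v 85% |
|---|---|---|---|
| 0% | 0 | 0.025 | 0.025 |
| 1% | 4 | 0.07 | 0.055 |
| 2% | 7 | 0.17 | 0.11 |
| 3% | 11 | 0.35 | 0.20 |
| 5% | 19 | 0.82 | 0.51 |

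If both arms lose the same share of failures, the probability stays between 0.015 and 0.024 for removals of 1% to 5%, so there is no inflation.

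**The case against.** The strongest reply is that the text does not say follow-up ends. Treatment runs for weeks, with a cast in place and pins to remove, so discontinuation could refer to that phase. Trial duration promises two years for everyone. A journal article also commonly leaves follow-up after discontinuation, and the handling of missing outcomes, to the full protocol.

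Much of this stands, and it rules out several stronger readings that a reader might infer:

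- **That the 24-month score is never collected.** No sentence says so, and one points the other way. The supportable statement is that collection is not secured.
- **That the worst cases as a group are lost.** A child with a poor score or malalignment but neither trigger stays in. Only serious adverse events related to the trial count.
- **That no analysis of all randomised children could help.** The analysed outcome is binary, so a child without a 24-month visit can be counted as a non-success. That is a convention and does not replace the observed score, but it is available.
- **That the hidden difference is −4.75 points.** This is the extreme of an assumed range. It needs one-sided removal and failure of every removed child.

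The reply does not remove the contradiction. The rule is stated in mandatory terms and is not a detail left out, and it disagrees with another sentence of the same article.

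**Conclusion.** The concern holds in a limited form. The Discontinuation criteria contradict Trial duration on whether a child is followed after a non-permitted treatment or a trial-related serious adverse event. That leaves the 24-month Cooney score and the later course of complications unsecured for children whose removal is related to outcome.

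How large the bias would be cannot be known from the article, which gives neither success rates nor removal rates. Under the stated assumptions it lies between 0 and −4.75 points against a 5-point margin. The error rate is inflated only if failures are removed more often from the cast arm than from the control arm. In that worst case a few children are enough: about 7 failures removed from the cast arm alone raise the one-sided error from 0.025 to 0.11 or 0.17, depending on the assumed rates.

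Continued follow-up does not by itself change the primary result. The primary population is per-protocol, and these children might still be excluded from it as major violators; the article does not say whether they would be. What follow-up secures is the data without which no analysis of all randomised children can use their actual outcomes.

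**What to change.** 1. Reconcile Discontinuation criteria, Trial duration and Secondary endpoint. State that discontinuation ends the allocated treatment only, and that every randomised child continues the scheduled 3-, 12- and 24-month assessments unless consent to follow-up is withdrawn.
2. Record the reason and date of each discontinuation, so that the two arms can be compared on it.
3. Include these children in an analysis of all randomised patients, reported alongside the per-protocol analysis. In a sensitivity analysis, count those whose 24-month outcome is still missing as non-success.

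Decisions about a child's care are not touched. The cost is a short amendment and some extra effort to bring these children back. The visits are already in the schedule, and the sample size does not change. When the article was submitted, 42 of 742 children had been included, so the change could then have covered the remaining 700 from entry.

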### Treatment

Group 1 (experimental/conservative): Plaster immobilization without any reduction for 4 weeks, the kind of plaster (Paris, cast, forearm, upper arm or sandwich) is to be determined by the treating clinic. As no reduction is performed, no anesthesia is needed. After the fracture is immobilized with the plaster, the patient will leave the emergency department.

Group 2 (control): Closed reduction under anesthesia, percutaneous K-wire osteosynthesis with one or two wires (through physis or Kapandji), plaster (Paris, cast, forearm, upper arm or sandwich) is to be determined by the treating clinic. No other form of osteosynthesis is allowed. After the operation, the patient is treated on the ward for 1 or 2 days.

### Trial duration

The anticipated trial duration will be 60 months. Recruiting began in April 2014 and will be completed in March 2018. All patients will be monitored for 2 years.

### Number of patients

A total of 742 patients shall take part, with 371 per group. Recruiting is planned for 30 clinics.

### Primary endpoint

The primary endpoint is the Cooney Score after 24 months. If there is a visible malalignment, an X-Ray will be performed to confirm the exact degree of malalignement.

### Secondary endpoint

The secondary endpoints are as follows:Completed Cooney Score after 3 and 12 monthsCompleted questionnaires CHC-SUN and ZUF-8 after 3, 12 and 24 monthsMalalignment after 12 and 24 monthsSecond reductionNeed for reeapplied K-wire osteosynthesisGrowth disturbanceComplications (according to Dindo-Clavien 4)

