**Fig. 2 Fig2:**
[figure not shown]
Work flow

Children between 5 and 11 years come to the emergency department with angulated fractures of the forearm. If all criteria are fulfilled and informed consent is given, the patient will be randomized.

After inclusion into the trial, dependent on the randomization result, patients are treated conservatively with a plaster (experimental group/group 1) or prepared for reduction and osteosynthesis under anesthesia (control group/group 2). A cast similar to the experimental group is applied.

For both groups, the kind of cast used (upper arm, forearm, sandwich, cast, or plaster of Paris) does not influence outcome of bony healing. In all controls, physical examinations in order to rule out complications of cast and serious adverse events are performed.

Patients included into the experimental group (1) go home after their treatment and come back the next day for clinical control. At this time-point quality-of-life questionnaires (ZUF-8 and CHC-SUN modified) are handed out. After 7 days, a clinical and X-ray control are performed in order to rule out secondary dislocation. If there is uneventful course of treatment, the next visit will be 4 weeks later for the next clinical and radiological control. If complete healing of the fracture is achieved, the cast is removed. Once again quality-of-life questionnaires are handed-out. Patients begin movements of daily routine, and physical exercise is postponed for another 2 to 4 weeks.

Patients included in the control group (2) stay on the ward after the operation for 1 or 2 days. Parents are instructed how to clean pin(s) or to perform wound controls. Exact reduction and position of K-wires is documented either during the procedure or on the next day. Quality-of-life questionnaires are handed out. At the next visit 4 weeks later radiological control and pin removal are performed, so far bony healing is documented. Patients begin with movements of daily routine, and physical exercise is postponed for another 2 to 4 weeks. The next quality-of-life questionnaires are handed out.

Three months after trauma, a next clinical control as well as assessment of the Cooney score and quality of life (CHC-SUN and ZUF-8) is conducted [5, 11]. 12 and 24 months after trauma similar visits in order to assess the same parameters are scheduled.

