### Safety

Serious Adverse Events will be reported within 24 hours of the initial observation to the IZKS. An independent scientific advisory board will monitor and supervise the progress of the trial. Therapeutic complications will be documented and analyzed according to the Dindo-Clavien classification [4]. Tables and listing of adverse events will be provided.

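### The two re-intervention endpoints are worded for the operated arm only, so conversion from plaster to reduction or pinning has no endpoint of its own

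*Protocol article*

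**What the plan says.** The Secondary endpoint section lists, for the trial as a whole and without restriction by arm, Cooney scores and questionnaires, malalignment at 12 and 24 months, and then "24 monthsSecond reductionNeed for reeapplied K-wire osteosynthesisGrowth disturbanceComplications" (the line breaks were lost in the text), the last graded by Dindo-Clavien.

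The Treatment section gives Group 1 "Plaster immobilization without any reduction for 4 weeks" and no wire. Group 2 receives "Closed reduction under anesthesia, percutaneous K-wire osteosynthesis with one or two wires", followed by plaster.

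The Trial schedule foresees that plaster may fail to hold. For Group 1 it states: "After 7 days, a clinical and X-ray control are performed in order to rule out secondary dislocation". No listed endpoint names a reduction or pinning that follows from that check.

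Three other places bear on the point:
- **Discontinuation criteria:** a child leaves the trial if "a treatment is needed that is not allowed in the" protocol.
- **Power calculation/analysis:** the primary population is per-protocol, "comprising all randomized patients without major protocol violations" and with at least one measurement after intervention. The responder rule is "All patients presenting a Cooney Score of at least 90 after 24 months and, if clinically obvious, a radiologic displacement not exceeding 5" degrees. It has no re-intervention component.
- **Safety:** "Therapeutic complications will be documented and analyzed according to the Dindo-Clavien classification", and adverse events are tabulated and listed.

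**The concern.** The abstract and the Discussion name the benefit that the trial hopes to establish: if remodeling proves safe, children can be spared manipulation under general anesthesia, pinning and pin removal. How many Group 1 children nevertheless came to need a reduction or a pin is the most direct evidence on that claim.

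The two endpoints that look designed to count re-interventions are worded so that this event does not qualify. The operated arm can accrue events from the start. The plaster arm can do so only after a child has already been converted once and then needs a further procedure. A table of these items by arm would show a difference produced largely by the definition, in the direction that favors the experimental treatment. If converted children also dropped out of the per-protocol set, the primary analysis would not show the failures either.

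**Working it through.** The point is one of definition, and no figure in the document tests it. The first step sets the sections side by side. The second and third steps are illustrations only.

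**1. Which events qualify, reading the labels literally**

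| Event | Group 1 (plaster, no reduction, no wire) | Group 2 (reduction and wire) |
|---|---|---|
| First reduction after the allocated treatment | Not a second reduction: not counted | Not applicable, already done as allocated treatment |
| First pinning after the allocated treatment | Not a reapplied wire: not counted | Not applicable, already done as allocated treatment |
| Repeat reduction | Counted only if the child was reduced once already | Counted |
| Repeat pinning | Counted only if the child was pinned once already | Counted |

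The corresponding failure of the allocated treatment, an unplanned procedure on the same fracture, is thus counted in Group 2 and not in Group 1.

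**2. Number of uncounted events**

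Inputs: 371 children per group (Number of patients section) and a conversion share *f* in Group 1, which is assumed because the document gives none. Converted children = 371 × *f*.

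- *f* = 2%: 371 × 0.02 = 7.4, about 7
- *f* = 5%: 371 × 0.05 = 18.6, about 19
- *f* = 10%: 371 × 0.10 = 37.1, about 37
- *f* = 15%: 371 × 0.15 = 55.7, about 56

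Read literally, each of these gives zero first conversions under the two endpoints.

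To see how far a comparison could move, assume also 3% re-intervention in Group 2 (371 × 0.03 = 11.1, about 11). The two-sided Fisher exact test on 371 per arm, a test chosen here and not specified in the article, gives:

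| Group 1 vs Group 2 events | Assumption for Group 1 | p |
|---|---|---|
| 0 vs 11 | As worded, whatever the true rate of first conversions | 0.0009, fewer in Group 1 |
| 15 vs 11 | Counted alike, 4% conversion | 0.55 |
| 19 vs 11 | Counted alike, 5% conversion | 0.19 |
| 30 vs 11 | Counted alike, 8% conversion | 0.003, more in Group 1 |

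The literal count stays at 0 vs 11 in every row. The symmetric count moves with the assumed rate.

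**3. Possible reach into the primary analysis**

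Inputs: the margin of −5 percentage points (Power calculation/analysis section) and an assumed 95% responder rate in Group 2 and in unconverted Group 1 children. If converted children counted as non-responders, the arm difference would shift by 0.95 × (1 − *f*) − 0.95 = −0.95 × *f*:

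- *f* = 2%: −1.9 points
- *f* = 5%: −4.75 points
- *f* = 10%: −9.5 points
- *f* = 15%: −14.25 points

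If they were dropped from the per-protocol set, the shift would be 0. If they were kept and assessed by the responder rule as it stands, the result would depend on their Cooney score and alignment at 24 months. A child pinned after failed plaster could then count as a responder in Group 1, with the conversion visible in neither the primary analysis nor the two secondary items.

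**The case against.** Four objections carry weight.

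**Failure of plaster is not invisible.** A reader might infer that it is recorded nowhere. The documents do not support that. Complications, adverse events, malalignment at 12 and 24 months and growth disturbance apply to both arms, and the responder rule can register a poor result if the child stays in the analysis. This stands. But these routes are indirect: a pooled complication table does not yield a conversion rate, and a child successfully converted may show no malalignment later.

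**Exclusion from the primary analysis is not stated.** A reader might infer that every converted child is discontinued and removed. The article does not say that a later reduction in Group 1 is a treatment outside the protocol, nor that conversion is a major violation. The schedule's wording about an uneventful course implies that some other path exists, which a condensed article need not set out. This stands: exclusion is a plausible reading, not an established one.

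**The labels are terse.** A second reduction may have been meant as a secondary one, that is, any later reduction, which would take in Group 1. The document does not settle this. It is harder to read a reapplied wire that way. Operational definitions may be left to a fuller document, but the labels that such a document would inherit are stated here, and as stated they do not fit both arms.

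**No between-arm test of these items is specified.** The stated comparison concerns the primary endpoint, and the two items might simply be described. It would therefore be too strong to say that the trial will report a false advantage. What remains is that any reading across arms would be tilted. If the items are meant for the operated arm alone, conversion from plaster still lacks an endpoint.

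**Conclusion.** The point holds as a fault in the wording of two secondary endpoints. As written they presuppose a reduction or wire that only Group 2 receives, so they are not comparable between arms, and a first reduction or pinning after failed plaster has no endpoint of its own. The direction follows from the wording: a comparison would lean toward the conservative arm.

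The size is not known. The counts of 7 to 56 children, the Fisher results and the shifts of −1.9 to −14.25 points all rest on assumed event rates, and the shifts also on an assumed 95% responder rate and on scoring converted children as non-responders. They show what the definition could hide and are not evidence from the documents. The reversal from an apparent benefit to an apparent harm needs the 8% conversion rate; at 4% or 5% the symmetric count shows no significant difference.

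The primary hypothesis, margin and sample size do not depend on these two items. The change is worth making because the uncounted event is the one that the trial's stated benefit turns on.

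**What to change.** Replace the two items with one endpoint defined alike in both arms: any unplanned reduction or osteosynthesis of the study fracture after the initial allocated treatment. In Group 1 this captures conversion, and in Group 2 a repeat reduction or pinning. State that planned pin removal does not count. Report it by allocated arm in all randomized children, whatever their status in the per-protocol set.

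State also whether conversion in Group 1 counts as a major protocol violation, so that its effect on the primary population is clear.

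The endpoint records what happened and sets no rule on when to re-intervene. The cost is one reworded endpoint and one CRF item, with no extra visits. At submission 42 of the planned 742 children had been included, so few records would need to be checked retrospectively.
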